### Statistical analyses

We will use methods suitable for cluster trials with relatively few clusters, analysing cluster-level summary measures (proportions) of all binary outcomes to account for between-cluster variation, and reporting crude and covariate-adjusted results [21]. We first will convert all Likert and numeric scale outcomes into binary scale outcomes. As laid out above, the four-point Likert scale outcomes will be dichotomised by combining the first two categories and then the final two categories. The two 5-point Likert scale outcomes will be dichotomised by combining the first two categories and then the final three categories. The five-point numeric scale outcomes will be dichotomised by combining the first three categories and then the final two categories. For all outcomes, we will first estimate the crude intervention effect as the difference between the mean intervention arm and mean control arm cluster-level outcome proportions (i.e. a risk difference), and we will estimate the 95% confidence intervals and *p* value associated with this effect size estimate using an independent *t*-test.

We will then estimate covariate-adjusted results using a two-stage method [21]. First, using a logistic regression model, we will model the effects of our covariates of interest on the individual-level binary outcomes, while excluding the effect of treatment. We will then use the individual-level model predicted values and the individual-level observed values for each outcome to calculate covariate-adjusted cluster-level difference residuals. Lastly, we will use these values in place of cluster-level summary outcome measures to estimate covariate-adjusted risk differences, and again use *t*-tests to estimate the associated 95% confidence intervals and *p* values. We will adjust outcomes for covariates as shown in Table 1. In addition, using the methods outlined in Hayes & Moulton [21] for analysing cluster-level effect modification, we will assess whether the treatment effect differs for the primary outcome between the following subgroups: Ethiopia vs Vietnam and switchers vs adopters.

**Table 1 Tab1:** Planned covariate adjustment for covariate-adjusted analyses

Outcome	Covariates adjusted for
Primary (LAPM uptake among FP switchers and adopters)	1–8
Proportion of clients recommended a LAPM by their provider	1–8
How well clients felt providers listened to their needs	1–8
How relevant clients felt the method(s) recommended by providers were to their needs	1–8
How well clients felt they understood the potential side effects of their chosen method	1–3, 5–6, 8
How clients felt about the amount of information given to them during counselling sessions	1–8
How clients felt about the length of their counselling sessions	1–8
How clients rated their experience of receiving counselling	1–7
Proportion of adopters or switchers who chose a LAPM following their FP counselling session and reported still using the same method at 4 months	1–9
Proportion of adopters or switchers who chose a LAPM following their FP counselling session and who report that they plan to continue using their current method	1–9
Proportion of clients who chose any short-acting FP method following their FP counselling and reported still using the same method at 4 months	1–9
Proportion of clients who chose any short-acting FP method following their FP counselling and who report that they plan to continue using their current method	1–9
How clients rated their overall satisfaction with the FP method they received following their FP counselling at 4 months	1–8

*FP* family planning, *LAPM* long-acting or permanent method of contraception, *MSI* Marie Stopes International

Covariates: (1) country (Ethiopia or Vietnam), (2) client age, (3) client education level (none, primary, secondary, college or higher), (4) marital status (single or no regular partner, regular partner, married, divorced or separated, refused to say), (5) FP intentions (trying to become pregnant now or within 1 year, aiming to become pregnant within 2+ years, do not want any or anymore children or do not know), (6) current FP usage (currently use LAPM, currently use short-acting or natural method or unsure what method, not currently using any FP method or have never used any FP method), (7) reason for visiting MSI clinic (seeking FP health care, seeking abortion health care or seeking other health care), (8) overall initial rating of FP counselling experience (1–5, where 1 is “bad” and 5 is “good”), (9) overall rating at 4 months of satisfaction with the method received (1–5, where 1 is “bad” and 5 is “good”)

We will analyse client data based on the original allocation of the clinic that they attended, but we will also conduct sensitivity analyses where we will analyse client data based on how the clinic they attended actually participated in the study (i.e. as either an intervention or control clinic). Prior to the analyses, we will assess the level and pattern of any missingness in outcome or covariate data and investigate the likely causes of missingness. We will conduct complete case analyses of outcomes unless these investigations indicate there is likely to be substantial bias introduced, in which case we will use multilevel multiple imputation methods of analysis [22]. We will make our primary inferences about the statistical significance of the results via formal hypothesis testing. Statistical significance will be at the 5% level based on the (two-sided) *p* values estimated for all outcomes obtained from the covariate-adjusted analyses, as these are likely to have more power and reduced bias (when estimating the treatment effect) than the crude analyses, which will help us to understand how any imbalances in covariates between treatment arms influence the treatment effect [23]. We will evaluate clinical significance based on the effect size estimates and their 95% confidence intervals, with an increase of 10.5 percentage points or more in the primary outcome seen as clinically significant. We will not adjust secondary outcomes for multiple testing. No interim analyses are planned. We will specify our planned analyses in a statistical analysis plan prior to analysis, which will be published with the results.

We will analyse the observation checklist outcomes using survey methods appropriate for the clustered design of the study [24], via the *survey* [25] package in the statistical software R. We will primarily analyse survey checklist outcomes descriptively, either as percentages (categorical outcomes) or as means (continuous outcomes), making inferences about the plausible range of true values for outcomes based on their 95% confidence intervals. We will calculate outcome results from the pooled data and for each country separately, exploring differences in outcomes between countries based on outcome point estimates and 95% confidence intervals.

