Marie Stopes International (MSI) seeks to help women choose a contraceptive method that suits their individual lifestyles and medical needs. In the past, MSI provided FP counselling training for providers that focused on the delivery of information from providers to the clients. More recently, MSI’s training has changed, placing greater emphasis on meeting the clients’ contraceptive needs and preferences. Currently, MSI providers use flipcharts to support their FP counselling sessions. However, providers typically use the flipcharts intermittently and there is substantial variation between providers’ consideration of clients’ circumstances and the suitability of methods recommend. This can result in providers offering unnecessary or an overwhelming number of options to clients, or just offering a subset of suitable options.

Therefore, given the increasingly affordable access to tablet computers, the Medical Development Team at MSI developed a tablet-computer based digital job aid, known as the Digital Counselling Application (DCA). The aim of DCA is to provide a tool that: (1) promotes interaction between providers and clients by forcing providers to ask clients a structured and systematic series of questions and (2) provides the client with a personalised list of recommended methods, based on an algorithm that uses information about the client’s situation, which the provider enters into DCA, removing the need for the provider to do this in their head (and thereby provide advice of varying quality of specificity). Women’s unmet need for modern methods, including LAPMs, is significantly associated with women’s education and empowerment, the quality of client counselling, partner discussions and exposure to media [18, 19].

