In recognition of these factors, the intervention aims to support the uptake of modern methods through quality client-centred counselling. The intention is to standardise the quality of care in FP counselling to inform clients and empower them to select their preferred method. We hypothesise that DCA will offer a more client-focused counselling process, increasing providers’ consideration of clients’ circumstances and needs, reducing bias in provider recommendations, limiting discussion of all possible FP methods but expanding discussion on client-preferred methods (as ranked by DCA) designed to suit clients’ needs and preferences. This is anticipated to improve users’ counselling experience and increase clients’ readiness to consider and accept a LAPM. Our primary objective is, therefore, to evaluate the effects of DCA on LAPM uptake among clients attending FP counselling at MSI clinics in Ethiopia and Vietnam. We will also explore any effect of the DCA-led client-centred counselling on continuation rates of LAPM uptake, since providers are actively prompted to provide an upfront discussion of the side effects in advance of LAPM uptake compared to traditional counselling. The trial is also supported by a qualitative exploration of providers’ and clients’ experience of DCA, to identify where and how DCA can be improved.

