We will also conduct a structured observation survey of provider–client interactions during FP counselling sessions in intervention arm clinics. For this survey, providers will be asked to participate by a researcher, who will seek their written informed consent. The survey will then be carried out in each participating clinic over the course of a day or two, with all clients attending the clinics for FP counselling being asked to participate in the survey by the researcher, who will again seek their written informed consent. An overview of the different quantitative and qualitative components in the trial and their interlinkages is provided in Fig. 2.

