### Control

In the control arm, clinics providers will continue to offer the usual provider–client FP counselling service. Typically, this means providers offer an overview of most or all methods before asking the client to select one. However, if providers in control arm clinics have not received MSI’s existing standard training on client-centred counselling within the last 18 months then they will receive refresher FP training. Providers in both the control and intervention arms will have access to their existing job aids, such as posters, diagrams, flipcharts, anatomy models and the WHO contraceptive wheel. Only providers in the intervention arm clinics will have access to and be given training on DCA and the tablets used to run DCA.

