### Secondary outcomes

The following secondary outcomes use data from initial client exit telephone interviews:Proportion of clients recommended a LAPM by their provider.How well clients felt providers listened to their needs, measured on a four-point Likert scale: (1) listened well, (2) listened quite well, (3) did not listen well or (4) did not listen at all well.The degree to which clients felt the methods recommended by providers were relevant to their needs, measured on a four-point Likert scale: (1) very relevant, (2) a bit relevant, (3) not very relevant or (4) not at all relevant.How well clients felt they understood the potential side effects of their chosen method, measured on a four-point Likert scale: (1) understand very well, (2) understand quite well, (3) do not understand well or (4) do not understand at all well.How clients felt about the amount of information given to them during counselling sessions, measured on a five-point Likert scale: (1) much too little, (2) slightly too little, (3) about right, (4) slightly too much or (5) much too much.How clients felt about the length of their counselling sessions, measured on a five-point Likert scale: (1) much too short, (2) slightly too short, (3) about right, (4) slightly too long or (5) much too long.How clients rated their experience of receiving counselling, measured on a five-point numeric scale where 1 was “bad” and 5 was “good”.

The following secondary outcomes use data from client 4-month telephone interviews:Proportion of adopters or switchers who chose a LAPM following their FP counselling session and reported still using the same method at 4 months.Proportion of adopters or switchers who chose a LAPM following their FP counselling session and who report that they plan to continue using their current method.Proportion of clients who chose any short-acting FP method following their FP counselling and reported still using the same method at 4 months.Proportion of clients who chose any short-acting FP method following their FP counselling and who report that they plan to continue using their current method.How clients rated their overall satisfaction with the FP method they chose following their FP counselling at 4 months, measured on a five-point numeric scale where 1 was “bad” and 5 was “good”.

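### The cut of the two five-point scales pools 'about right' with 'too much' or 'too long', so these secondary outcomes measure only 'too little' or 'too short'

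*Protocol article*

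**What the plan says.** The protocol article, under Secondary outcomes, defines two five-point Likert items from the exit telephone interview. Amount of information is scored "1) much too little, (2) slightly too little, (3) about right, (4) slightly too much or (5) much too much". Session length is scored "1) much too short, (2) slightly too short, (3) about right, (4) slightly too long or (5) much too long".

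Under Statistical analyses it states: "We first will convert all Likert and numeric scale outcomes into binary scale outcomes". For these two items the rule is: "The two 5-point Likert scale outcomes will be dichotomised by combining the first two categories and then the final three categories". The other scales have their own rules. The four-point items are split 1–2 versus 3–4, and the five-point numeric ratings 1–3 versus 4–5. So there is no doubt which outcomes are meant. The same section applies two-sided 5% significance to the covariate-adjusted results of all outcomes.

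Three statements bear on what DCA is expected to change:

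- On current practice, the Background says: "This can result in providers offering unnecessary or an overwhelming number of options to clients".
- On how DCA should work, it includes: "limiting discussion of all possible FP methods but expanding discussion on client-preferred methods".
- Under Control, usual care typically means that "providers offer an overview of most or all methods before asking the client to select one".

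**The concern.** The four-point items and the numeric ratings run from one extreme to the other, so any single cut keeps better answers on one side and worse answers on the other. The two five-point Likert items do not. Both ends are complaints and the satisfactory answer lies between them. A single cut point on such a scale must pool the satisfactory answer with one kind of complaint. Here it is pooled with 'too much' or 'too long'.

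That matters because part of the stated rationale concerns this side. If usual care covers most or all methods and DCA narrows the discussion, one expected change is from 'too much' to 'about right'. If a structured tablet session instead felt long, clients would move from 'about right' to 'too long'. Neither change can appear in the planned outcomes, although each outcome will carry a formal test and a published conclusion about client experience.

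**Working it through.** **Inputs from the documents.** The category labels (Secondary outcomes), the cut 1–2 versus 3–5 (Statistical analyses), and 18 and 17 clinics with 75 clients each and a between-cluster coefficient of variation of 0.2 (Sample size). The documents give no category distribution and no power figure for these two items.

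**Step 1: what the planned outcome measures.** Write L for the share answering 1–2, R for the share answering 3 and H for the share answering 4–5, so that L + R + H = 1. The planned proportion is R + H = 1 − L. The between-arm risk difference is therefore

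Δ(planned) = ΔR + ΔH = −ΔL.

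- If L is the same in both arms, Δ(planned) = 0 for any split between R and H. This needs no assumption about the distribution.
- A client who moves from 1–2 to 3 and one who moves from 1–2 to 4–5 contribute equally.
- Covariate adjustment does not recover the contrast. The observed values entering the two-stage method are the same binary values, so 3, 4 and 5 are already merged.

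**Step 2: the plan's own power figure, to check the formula.** The variance of a cluster proportion is p(1−p)/m + (kp)², with m = 75 and k = 0.2.

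- Control, p = 0.40: 0.0032 + 0.0064 = 0.0096.
- Intervention, p = 0.505: 0.00333 + 0.01020 = 0.01353.
- SE = √(0.01353/18 + 0.0096/17) = 0.0363, and 0.105/0.0363 = 2.89.
- Power from the noncentral t with 33 degrees of freedom is 80.2%, against the stated 80%. The formula reproduces the plan's figure.

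**Step 3: illustration with assumed shares.** All percentages in this table are assumptions, in category order 1/2/3/4/5.

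| Case | Control | DCA | Planned outcome (3–5) | 'About right' (3) | 'Too much' (4–5) |
|---|---|---|---|---|---|
| A | 5/10/55/20/10 | 5/10/70/10/5 | 85 vs 85: 0 | 55 vs 70: +15 | 30 vs 15: −15 |
| B | 5/10/65/15/5 | 5/10/75/7/3 | 85 vs 85: 0 | 65 vs 75: +10 | 20 vs 10: −10 |
| C | 5/15/50/20/10 | 5/5/50/25/15 | 80 vs 90: +10 | 50 vs 50: 0 | 30 vs 40: +10 |

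In A and B a crude test of the planned outcome rejects only at its 5% false-positive rate. With the Step 2 formula, and the coefficient of variation of 0.2 applied to the rarer category (a further assumption), 'about right' versus the rest has power of about 99% in A and about 94% in B. In C the planned outcome rises by 10 points although no more clients are satisfied and 10 points more complain of too much.

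**Step 4: does another stated analysis fill the gap?** No ordinal or three-category analysis is given. The observation survey records session length and the number of methods recommended, but it is described as a "structured observation survey of provider–client interactions during FP counselling sessions in intervention arm clinics". The randomisation section speaks of selecting providers from all participating clinics. Even on that reading, the survey is analysed descriptively, with no comparison between arms.

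**The case against.** The strongest reply is that too little information is also a documented failing of usual counselling. The Background says that providers may present only some of the suitable options, and the Intervention section says that side effects often go unmentioned. The planned cut measures that failing correctly. This stands: the outcomes are one-sided, not meaningless.

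A reader might infer that the plan scores overload as an improvement, or will give a wrong-signed result. The documents do not support that. They say which categories are combined but never call 3–5 favourable. Reported as the proportion saying 'too little' or 'too short', the result would be correct. A longer session also raises the planned proportion only if fewer clients answer 'too short'. Case C misleads only someone who reads 3–5 as success.

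A reader might also infer that the trial as a whole cannot detect overload. That is too broad. Perceived relevance of the recommended methods and the overall counselling rating are compared between arms and could reflect it indirectly, and the qualitative work covers acceptability and time taken. None of these replaces the direct contrast.

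Finally, the statistical analysis plan is not shown and may use another cut. The article nevertheless states this one explicitly, so any difference would have to be reconciled.

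**Conclusion.** The concern holds as a fault in two of the twelve secondary outcomes. As defined, they cannot distinguish the best answer from the two 'too much' or 'too long' answers, and the contrast they lose is one side of what the protocol expects DCA to change. The zero effect for any shift within categories 3–5 is exact and rests on no assumption. Its practical size is unknown: if few clients choose 4 or 5, little is lost, and the shares and power figures above are illustrative only.

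The primary outcome, the sample size, the randomisation and the data collected are unaffected. All five categories are recorded, so the fault can be repaired in full. This is a should-fix; a stronger rating would need the article to treat 3–5 as favourable, which it does not.

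**What to change.** Replace the sentence on the two five-point Likert items. For both, define the binary outcome as 'about right' (3) versus any other answer (1, 2, 4, 5). Because that outcome pools opposite complaints, also report by arm the proportions answering 'too little/short' (1–2) and 'too much/long' (4–5), with risk differences and 95% confidence intervals from the same cluster-level method. The 1–2 proportion is the complement of the planned outcome, so nothing now planned is lost.

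The cost is one sentence and two extra proportions per item in the results table. No new data are needed. The change should be written into the statistical analysis plan before analysis, which the protocol article already commits to, so that the new cut cannot look data-driven. If that plan already uses a different cut, the two documents must be reconciled.

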### Primary outcome

The primary outcome will be reported LAPM uptake. This is defined as the proportion of switchers and adopters who report choosing a LAPM following FP counselling (rather than a short-acting method). Switchers are clients using any FP method at the time of counselling who then change to any other FP method following counselling. Adopters are clients who are not using any FP method at the time of counselling but who decide to start using any FP method following counselling. LAPM methods include contraceptive implants, IUDs, intrauterine systems and tubal ligation, with all other FP methods considered short-acting methods. This outcome will be calculated from data collected at the initial telephone exit interview, and its accuracy is, therefore, dependent on the accuracy of clients’ responses. This primary outcome (reported LAPM uptake) is already used by MSI as a clinic performance indicator, making it feasible to collect this information. It is also a key indicator of FP practices supporting sustainable development goals 3 and 5.

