### Sample size

Based on logistical considerations, we assume that we can recruit 75 clients per clinic across 35 clinics during the recruitment period. Based on routine MSI clinic data, we estimate that the primary outcome of LAPM uptake in switchers and adopters is currently typically around 40%. We, therefore, estimate that we will have 80% power to detect an absolute increase in LAPM uptake from 40% to 50.5% (judged by trial researchers and MSI FP experts to be a sufficiently small, clinically important difference for these contexts) at a 5% level of statistical significance, assuming a between-cluster coefficient of variation of 0.2 (based on prior MSI routine data), with 18 clinics in the intervention arm and 17 in the control arm, and 75 clients recruited per clinic [20].

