### Quantitative data collection and management

As MSI client data currently collected by clinics are not available for research, we prepared data collection tools to collect the required outcome data. There will be three data collection processes, all conducted by researchers. First, to collect data on our quantitative primary and secondary outcomes, as well as a range of relevant socio-demographic covariate data, researchers will conduct initial client exit telephone interviews using a data collection form. Second, researchers will also collect additional client outcome data 4 months after their FP counselling sessions on related secondary outcomes via further telephone interviews using another data collection form. Third, researchers will record outcomes from the structured provider observation survey via a structured observational checklist tool.

Data management will initially be the responsibility of the in-country study leaders. For each data collection process, an SPSS database will be created with consistent coding and design, and this will be duplicated for use across countries. The databases will then be collated and merged by the study statistician, and checked for quality, accuracy and completeness using standard data validation methods, such as range and logic checks. Errors, anomalous values and missing values will then be explored along with in-country MSI staff against original data forms, to clean and correct the databases where possible before the database is locked. No personally identifying data will be collected in any data collection process, and so all stored client data will be anonymous. Consent forms will, however, be linkable to client data in the databases via a generic ID, and so will be stored in secure locked cabinets. Given the nature of the intervention and the very low risk of harms, it was decided not to have a data monitoring committee for the trial.

Both MSI (ER) and the University of Leeds (JW, JPH and LAB) will have full access to the final trial and associated study datasets, although only the University of Leeds will be involved in analysing the data.

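### A cheap gain in precision, not an error: the adjusted primary analysis leaves out each clinic's pre-trial LAPM uptake, which the sponsor may be able to supply

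*Protocol article*

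**What the plan says.** All places are in the protocol article.

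- **Primary outcome:** "This primary outcome (reported LAPM uptake) is already used by MSI as a clinic performance indicator".
- **Sample size:** from routine clinic data, "we estimate that the primary outcome of LAPM uptake in switchers and adopters is currently typically around 40"%. The calculation proceeds by "assuming a between-cluster coefficient of variation of 0.2 (based on prior MSI routine data"), with 18 and 17 clinics and 75 clients in each, and concludes that "we will have 80% power to detect an absolute increase in LAPM uptake from 40% to 50.5"%, "at a 5% level of statistical significance".
- **Statistical analyses:** "We will adjust outcomes for covariates as shown in Table 1". Table 1 assigns covariates 1 to 8 to the primary outcome: country, age, education, marital status, fertility intentions, current method, reason for visit and rating of the counselling. Country is the only one defined above the client. Primary inference uses the two-sided 5% level and the adjusted analysis, on the stated ground that adjustment should bring more power and less bias.
- **Randomisation:** only the 18:17 ratio is named as a restriction. No balancing on prior uptake is described.
- **Quantitative data collection and management:** "As MSI client data currently collected by clinics are not available for research, we prepared data collection tools".
- **Participants, recruitment and consent:** for clients lost to follow-up, basic demographics and chosen method will be taken from the clinic's routine records.

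**The concern.** The primary comparison is between 35 clinic-level proportions. When clinics differ a good deal among themselves, recruiting more clients per clinic cannot remove that part of the variance, but a predictor measured on the clinic can. The natural predictor is the clinic's own earlier value of the same outcome. The protocol says this quantity is tracked by clinic, and it used routine data to set the between-clinic variation, yet the otherwise detailed covariate list omits it. Covariate 6 records the client's current method, which describes the client and not the clinic's usual pattern of provision.

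Two things are at stake: precision, and protection against a chance difference between the arms in prior uptake. The protocol chose the adjusted analysis for the sake of power, so the omission matters on its own terms.

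**Working it through.** **Inputs (Sample size section):** p0 = 0.40, p1 = 0.505, k = 0.2, m = 75, 17 control and 18 intervention clinics, alpha 0.05. The two-sided test is from Statistical analyses.

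**1. Reproduce the stated power.** The variance of one clinic's proportion is p(1-p)/m + (kp)².

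- Control: 0.40 × 0.60/75 + (0.2 × 0.40)² = 0.00320 + 0.00640 = 0.00960.
- Intervention: 0.505 × 0.495/75 + (0.2 × 0.505)² = 0.00333 + 0.01020 = 0.01353.
- Clusters per arm by the unmatched formula: 1 + (1.96 + 0.84)² × (0.00960 + 0.01353)/0.105² = 17.47, against 17 and 18 planned.
- SE = √(0.00960/17 + 0.01353/18) = 0.0363. Noncentral-t power on 33 df = 80.2%.

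The stated 80% is correct with no covariate adjustment.

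**2. Between-clinic share.** Control 0.00640/0.00960 = 67%. Intervention 0.01020/0.01353 = 75%. Summed over arms, 0.0166/0.0231 = 72%.

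**3. Effect of a clinic-level baseline, compared with the crude analysis.** Let rho be the correlation between pre-trial and in-trial underlying clinic uptake. The documents give no value, so a range is assumed. Only the between-clinic part is multiplied by (1 - rho²); the binomial part stays. 32 df are used.

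| rho | SE | Power |
|---|---|---|
| none (crude, 33 df) | 0.0363 | 80.2% |
| 0.3 | 0.0351 | 82.7% |
| 0.5 | 0.0329 | 87.2% |
| 0.7 | 0.0292 | 93.6% |

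**4. Effect compared with the planned adjusted analysis.** Country is already covariate 1. If country removes a share g of the between-clinic variance, the remaining part is multiplied by (1 - g)(1 - rho²), where rho is now the residual correlation. g is not documented either.

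| g | Planned model | rho 0.3 | rho 0.5 | rho 0.7 |
|---|---|---|---|---|
| 25% | 87.2% | 89.1% (+1.9) | 92.3% (+5.1) | 96.4% (+9.2) |
| 50% | 93.8% | 94.9% (+1.1) | 96.5% (+2.7) | 98.4% (+4.6) |

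This table uses 32 df throughout. Deducting one more for the baseline (31 df) lowers the entries with a baseline by less than 0.1 point.

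**5. Chance imbalance.** At 40% and k = 0.2, underlying clinic uptake has an SD of 8 points. Under an 18:17 allocation with no balancing, the arm difference in prior uptake has SD 8 × √(1/17 + 1/18) = 2.7 points. By the normal approximation it is 3 points or more in either direction in about 27% of allocations. The target effect is 10.5 points. Country, already in the model, would take up part of such a difference.

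**The case against.** The strongest reply is that nothing here is wrong. The power claim stands without adjustment. Omitting a prognostic covariate in a randomised comparison introduces no bias and leaves the type I error intact. Eight covariates are already pre-specified. All of that stands, and it limits the point to an improvement.

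The gain could also be small.

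- **Country may do much of the work.** The Background describes very different method mixes in the two countries. If k = 0.2 is pooled over both (an assumption), an illustrative 12-point country difference gives (24/35)(11/35) × 0.12² = 0.0031, or 48% of the between-clinic variance of 0.0064.
- **The correlation may be weak.** The intervention aims to standardise counselling, and some control providers receive refresher training. Either could loosen the link between past and present uptake.

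Both caveats stand, which is why the size is given as a range.

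Availability is a further limit. A reader might infer that the sponsor demonstrably holds a usable baseline for all 35 clinics, so that the remaining noise is simply avoidable. The documents do not go that far. They do not say that k came from these clinics, and they state that clinics' client data are unavailable for research. That statement concerns client data, however. Routine figures were usable for the sample size, and routine records are to be used for clients lost to follow-up. A conditional recommendation therefore survives.

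A reader might also put power at 90.0% for rho 0.5 by shrinking the whole variance of a clinic proportion. That figure needs rho to be the correlation between observed proportions. If rho describes underlying clinic rates, binomial noise does not shrink and the figure is 87.2%. Either way, the crude analysis is not the right starting point when country is already in the model.

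**Conclusion.** The point holds as an inexpensive improvement to the decisive analysis. It does not show an error, a bias or a shortfall in power. Its firm part is that Table 1 omits prior clinic uptake, that uptake is tracked as a clinic indicator, and that on the plan's inputs most of the variance of a clinic proportion is between clinics.

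The size is conditional. Over rho of 0.3 to 0.7, the gain over the planned model is roughly 2 to 9 points of power if country removes a quarter of the between-clinic variance, and 1 to 5 points if it removes half. Neither rho nor the country share is documented. Client-level covariates 2 to 8 could absorb more and reduce the gain further. Whether the clinic figures can be released is inferred, not stated.

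**What to change.** Before analysis, in the statistical analysis plan that the protocol promises, add one covariate to the stage-one logistic model for the primary outcome and for the proportion of clients recommended a LAPM. The covariate is the clinic's aggregate LAPM uptake over a fixed period ending before randomisation. Deduct one further degree of freedom from the t-test, because this is a clinic-level covariate. State in advance how a clinic without a prior figure is handled, for example by using its country mean.

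Make this conditional on the sponsor being able to release the 35 aggregate figures. If it cannot, say so, explain how the coefficient of 0.2 was obtained, and reconcile the sections on recruitment, sample size and data management on what routine data may be used.

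The cost is one more line in the covariate table, 35 numbers and one degree of freedom, with no new client data. The routine indicator may be defined somewhat differently from the trial outcome. That would reduce the gain, but a covariate fixed before randomisation would not bias the comparison.
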